## Abstract

**Background:**

Recovery of upper limb function after stroke is poor. The acute to subacute
phase after stroke is the optimal time window to promote the recovery of
upper limb function. The dose and content of training provided
conventionally during this phase is however, unlikely to be adequate to
drive functional recovery, especially in the presence of severe motor
disability. The current study concerns an approach to address this
shortcoming, through evaluation of the SMART Arm, a non-robotic device that
enables intensive and repetitive practice of reaching by stroke survivors
with severe upper limb disability, with the aim of improving upper limb
function. The outcomes of SMART Arm training with or without
outcome-triggered electrical stimulation (OT-stim) to augment movement and
usual therapy will be compared to usual therapy alone.

**Methods/Design:**

A prospective, assessor-blinded parallel, three-group randomised controlled
trial is being conducted. Seventy-five participants with a first-ever
unilateral stroke less than 4 months previously, who present with severe arm
disability (three or fewer out of a possible six points on the Motor
Assessment Scale [MAS] Item 6), will be recruited from inpatient
rehabilitation facilities. Participants will be randomly allocated to one of
three dose-matched groups: SMART Arm training *with* OT-stim and
usual therapy; SMART Arm training *without* OT-stim and usual
therapy; or usual therapy alone. All participants will receive 20 hours of
upper limb training over four weeks. Blinded assessors will conduct four
assessments: pre intervention (0-weeks), post intervention (4-weeks), 26
weeks and 52 weeks follow-up. The primary outcome measure is MAS item 6. All
analyses will be based on an intention-to-treat principle.

**Discussion:**

By enabling intensive and repetitive practice of a functional upper limb task
during inpatient rehabilitation, SMART Arm training with or without OT-stim
in combination with usual therapy, has the potential to improve recovery of
upper limb function in those with severe motor disability. The immediate and
long-term effects of SMART Arm training on upper limb impairment, activity
and participation will be explored, in addition to the benefit of training
with or without OT-stim to augment movement when compared to usual therapy
alone.

**Trial registration:**

ACTRN12608000457347

## Background

Recovery of the upper limb after stroke is poor. Up to 80% of stroke survivors have
some upper limb disability during the acute to subacute phase after stroke. By
various estimates, only 5% to 20% demonstrate complete functional recovery [1-3]. Thus, stroke survivors with upper limb disability appear to be a
rehabilitation challenge. There is therefore, a pressing need to increase the
potential for functional recovery of the upper limb after stroke.

To drive recovery of function, it is recommended that training commence early and be
intensive, repetitive and task-oriented [4-6]. However, stroke survivors with severe motor disability are often unable
to participate in task-oriented training as they are incapable of generating levels
of volitional motor activity or control that are sufficient to engage in training
tasks [7]. Further compounding their situation is a lack of access to interventions
that make task-oriented practice possible [8]. It is therefore not surprising that priority is rarely given to upper
limb training by stroke survivors [9] or rehabilitation services [10-15] during inpatient rehabilitation. Yet, with stroke survivors spending up
to 25% of a physiotherapy session inactive [15], there appears to be considerable scope within current therapeutic
regimes to increase the delivery of task-oriented upper limb training.

To capitalise upon this opportunity, a non-robotic training device, the SMART Arm
(Sensori-Motor Active Rehabilitation Training of the Arm) (Figure 1), was developed to enable stroke survivors with severe upper
limb disability to undertake intensive and repetitive task-oriented training. The
device was specifically designed so that stroke survivors with little to no muscle
activity could practice reaching, a fundamental upper limb function, along a
straight-line path consistent with a normal reaching pattern. The device can be used
with or without electrical stimulation to the lateral head of triceps brachii to
augment elbow extension and enhance completion of the reaching task. To optimise the
potential for motor learning, this device incorporates elements critical to skill
acquisition, including active problem solving, augmented real-time feedback of
performance, task progression that is tailored to each individual, motivation and
encouragement.

**Figure 1 F1:**
[figure not shown]
SMART Arm.

To date, a 12-hour SMART Arm training program with or without electromyographic
(EMG)-triggered electrical stimulation to triceps has been investigated in chronic
stroke survivors with severe upper limb disability. Compared with the control group,
those who underwent SMART Arm training with or without stimulation showed a
significant improvement in upper limb function (improvement in MAS6 item 6 score)
that was sustained at 2 months follow-up [16], an improved ratio of triceps to biceps EMG activity during reaching [17], and greater corticospinal reactivity [18]. There were however, variations in the expression of additional benefits
derived from the use of EMG-triggered electrical stimulation. As this may have been
due to the use, by some individuals, of maladaptive patterns of EMG activity such as
co-contraction of biceps and triceps, that could nonetheless trigger stimulation, a
new method of outcome-triggered electrical stimulation (OT-stim) was developed.
Here, electrical stimulation is triggered when initial goal directed motion
surpasses an individualised threshold. Thus, assistance by means of electrical
stimulation (and reinforcement) occurs when the movement generated voluntarily is
commensurate with the desired outcome. In a pilot trial of SMART Arm with OT-stim
during inpatient rehabilitation, SMART Arm training (with or without OT-stim), led
to a significantly greater improvement in upper limb function as compared to usual
therapy alone [19]. In that these improvements were evident early after stroke, further
investigation within the context of a larger trial is warranted [20].

Thus, the primary aim of the current randomised controlled trial (RCT) is to
determine the ability of SMART Arm training with or without OT-stim compared to
usual therapy to improve upper limb function in stroke survivors with severe upper
limb disability undergoing inpatient rehabilitation. In addition, we will determine
the impact of the different training programs on upper limb impairment, activity and
participation.

## Methods/Design

### Design

A prospective, assessor-blinded, three group parallel RCT will be conducted with
75 stroke survivors with severe upper limb disability who are undertaking
inpatient rehabilitation (Figure 2).

**Figure 2 F2:**
[figure not shown]
Trial design.

### Location and setting

We plan to recruit stroke survivors from two inpatient rehabilitation services
located in Brisbane, Australia: the Princess Alexandra Hospital, with a six-bed
Acute Stroke Unit, located separately to a 78-bed Geriatric and Rehabilitation
Unit; and the Queen Elizabeth II Jubilee Hospital, which has a four bed Acute
Stroke Unit, co-located within a 24-bed Geriatric and Rehabilitation Unit.
Assessment and training will be undertaken in different areas of the same
site.

### Population

All stroke survivors admitted to the Acute Stroke Unit at each hospital will be
screened for eligibility. Participants will be eligible if they are adult stroke
survivors (>17 years) with a primary diagnosis of first-ever unilateral
stroke (ischaemic or haemorrhagic, including subarachnoid haemorrhage) less than
four months previously, which has been confirmed either radiographically (CT or
MRI) or clinically by the consulting physician; demonstrate severe upper limb
disability equivalent to a score of three or fewer out of a possible six points
(inability to hold the upper limb in position when placed at 90° shoulder
flexion in sitting) on the MAS item six; and are able to follow single-stage
commands, either with verbal instructions, demonstration or other non-verbal
cues.

Participants will be excluded if they are medically unstable as defined by the
medical registrar or by location in an acute medical ward; have upper limb
comorbidities that could limit their functional recovery (e.g., arthritis, pain,
other neurological disorders); have a contraindication to the use of (e.g.,
pacemaker insitu), or inability to tolerate, electrical stimulation (e.g.,
hypersensitivity or skin condition); have an infectious disease requiring the
use of personal protective equipment (e.g., methicillin resistant staphylococcus
aureus or vancomycin resistant enterococcus) or are unable to sit without
support.

### Randomisation and blinding

All participants will provide written informed consent. In the event that a
participant is unable to provide informed consent, consent will be sought from
their legal guardian. After completion of the initial assessment, participants
will be randomised to one of three dose-matched groups (two intervention and one
control). The intervention groups are SMART Arm training *with* OT-stim
(SMART Arm OT-stim) and usual therapy; SMART Arm training *without*
OT-stim (SMART Arm alone) and usual therapy. The control group will receive
usual therapy only. Concealed randomisation will be prepared by an offsite
investigator, not involved in recruitment, intervention or data collection,
using a computer generated random number sequence. Consecutively numbered,
randomly ordered opaque envelopes containing group allocation in permuted blocks
of four or six in a 1:1 ratio will be opened consecutively after baseline
assessment in the presence of the participant. Usual therapists will be informed
of group allocation.

Research assistants who enrol participants, and conduct pre, post and follow-up
assessments will be blinded to group allocation throughout the study.
Participant coding will not refer to group allocation and participants will be
instructed not to divulge information regarding their intervention to the
assessors during assessment. Participants, SMART Arm trainers and usual
therapists (physiotherapy and occupational therapy) will not be blinded to group
allocation. To control expectancy effects for participants and usual therapists,
it will be explained that it is not yet determined which therapy is more
effective.

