### Data analysis

Data analysis will be performed on an intention-to-treat basis using an alpha
level of 0.05. Descriptive statistics will be used to ensure comparability of
scores between groups at baseline, to describe performance at each phase and to
test whether the assumptions for use of parametric statistics have been met. If
the assumptions for F or t-tests are violated, equivalent non-parametric
statistics will be utilized. The main hypothesis will be tested using mixed
effects models, in a 3 group (SMART Arm + OT stim, SMART Arm alone, usual
therapy) × 4 phase (0, 4, 26, 52 weeks) model. This will be followed by
between-groups planned comparisons. All secondary outcomes will be analysed in a
similar manner.

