### Sample size

The principle endpoint is post intervention (4 weeks). Our previous RCT
demonstrated that stroke survivors using the SMART Arm alone or with electrical
stimulation demonstrated significant improvements in MAS-6 scores compared to
the control group [16]. On this basis, we estimate a mean improvement of 1.8 (SD 2) in the
usual therapy group, 2.91 (SD 2) in the SMART Arm alone group and 3.91 (SD 2) in
the SMART Arm with OT-stim group. To achieve 80% power and a significance of
0.05 with pairwise comparisons, 22 subjects are required per group, to total 66
subjects. A 15% dropout rate will be allowed to account for withdrawals, thus 25
subjects will be recruited per group, totalling 75.

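### The randomisation text describes a two-arm block scheme (blocks of four or six, 1:1) for a three-arm trial, so it neither defines nor guarantees equal groups

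*Protocol article*

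**What the plan says.** In the protocol article, Randomisation and blinding, participants "will be randomised to one of three dose-matched groups (two intervention and one" control). Later in the same paragraph the envelopes are said to hold allocations in permuted blocks "of four or six in a 1:1 ratio will be opened consecutively after baseline" assessment. An offsite investigator with no part in recruitment, treatment or data collection prepares the sequence.

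The Sample size section asks for equal groups. It gives "0.05 with pairwise comparisons, 22 subjects are required per group, to total 66", allows for 15% dropout, and concludes that 25 "subjects will be recruited per group, totalling 75".

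Nowhere does the article give a 1:1:1 ratio, a deliberately unequal ratio, a randomisation in two stages, or a rule for the fourth place in a block of four.

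**The concern.** Both block sizes divide by two and the ratio has two terms, so the sentence reads as a scheme for a two-arm trial. Applied to three arms it is incomplete: whoever builds the list must decide what to do with the place left over in each block of four, and different decisions give materially different lists.

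Blocking is the only balancing device the article describes. If it does not balance the three groups, the planned 25 per group has no support from the allocation method. The margin between 25 recruited and 22 required is only three per group, and dropout is meant to use it. A reader also cannot verify from the text that a given list follows the plan.

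This is not a detail left to a fuller document. The article states the block sizes and the ratio, and what it states conflicts with its own number of groups.

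**Working it through.** **Inputs.** Three groups; blocks of four or six; ratio 1:1 (Randomisation and blinding). 22 evaluable and 25 recruited per group, 75 in total; 15% dropout; SD 2; expected improvements 1.8, 2.91 and 3.91 (Sample size). Assumptions of mine: block sizes four and six equally likely, and two-sided tests at 0.05, since the article does not state sidedness.

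**The plan's own figure.** 22 × 1.15 = 25.3, which rounds to 25; 22 / 0.85 = 25.9, which would round up to 26. The stated 25 per group is reproduced by the first route and is within one of the second. Equal allocation to three groups is clearly intended.

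**Divisibility.** 6 = 3 × 2, so a block of six holds the three groups 2:2:2. 4 = 3 × 1 + 1, so a block of four leaves one place over. Both 4 and 6 are even, which fits two arms.

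**What a list of 75 looks like.** Three ways of filling a block of four were simulated (8,000 to 20,000 lists each; blocks of six always 2:2:2):

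| Filling of a block of four | Exactly 25/25/25 | Mean gap, largest minus smallest | A group below 22 before dropout |
|---|---|---|---|
| One of each group plus a random extra | about 10% | 2.8 | under 1% |
| Extra place always to the same group | under 0.1% | about 7.9 | about 20% |
| 2:2 between two groups, third omitted | about 1% | 5.4 | about 26% |

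The second row can be checked by hand. The mean block size is (4 + 6) / 2 = 5, so 75 places use about 15 blocks, 7.5 of each size. The favoured group gets 7.5 × 2 + 7.5 × 2 = 30, and each of the others 7.5 × 1 + 7.5 × 2 = 22.5.

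**Effect on power.** For a pair of groups at 22 and 28 instead of 25 and 25 (t-test, SD 2, two-sided 0.05):

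- difference 3.91 − 1.8 = 2.11: 95.5% becomes 95.2%
- difference 2.91 − 1.8 = 1.11: 48.5% becomes 48.0%
- difference 3.91 − 2.91 = 1.00: 41.0% becomes 40.5%

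For two groups of 22.5, as in the second filling, the variance factor is 2/22.5 = 0.0889 against 2/25 = 0.0800. The ratio is 1.11, so the standard error is about 5% larger (√1.11 = 1.05).

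**Schemes that fit three groups.** With 1:1:1 in blocks of 3 and 6, the gap at 75 is at most 2 and exact balance occurs in about 80% of lists. With blocks of 6 and 9, the gap is at most 3 and exact balance occurs in about 61%.

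**The case against.** The best defence is that little may follow. Blocks of six suit three groups. With a randomly placed fourth slot each group still averages 25, no block omits a group, and power hardly moves. Allocation is concealed and prepared offsite, and unequal numbers do not bias a randomised comparison. The sentence may be a slip in the article, with a sound list behind it. All of this stands as a limit on the consequence. None of it makes the sentence correct.

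Three stronger readings are tempting, and the documents do not support them:

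- A reader might infer that the scheme cannot deliver 25 per group. It can: the random-extra filling gives exactly that in about 10% of lists and 25 on average. Exact equality is also the wrong test, because blocks of 6 and 9 reach it in only about 61% of lists. What counts is whether the gap is bounded and the scheme defined.
- A reader might infer that allocation is confounded with calendar time. Whole blocks omit a group only under the 2:2 filling, which the article does not state. The 26% figure depends on the same assumption.
- A reader might infer that the list in use is faulty. The list is not shown, so this cannot be known.

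**Conclusion.** The point holds as a contradiction within the article: a two-arm block scheme is given for a three-arm trial with equal planned groups. That part is arithmetic and rests on no assumption.

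The consequence is conditional. It runs from mild (mean gap 2.8, a group below 22 in under 1% of lists) to material (mean gap 5.4 to about 7.9, a group below 22 before any dropout in about 20% to 26%), according to a filling rule that the text leaves open. These figures assume block sizes four and six equally likely and a list cut at 75. The loss of power is small under the mild filling. The scheme is wrongly specified and needs correcting, but no loss of validity has been shown.

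**What to change.** Replace the sentence with 1:1:1 allocation to the three groups in randomly varied permuted blocks whose sizes are multiples of three, for example 3 and 6, or 6 and 9.

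The abstract describes the trial as under way, so the offsite investigator should also check the existing list, which can be done without breaking concealment:

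- If the list is already 1:1:1 in multiples of three, correct the sentence only.
- If it contains blocks of four, regenerate the unused part under the corrected rule, and report the change and the point in the sequence at which it took effect.

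The cost is one sentence of text, one check of the list and, at most, a new computer-generated sequence with envelopes for the participants not yet randomised.

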### Intervention

All participants will receive 20 hours of upper limb therapy, comprising 60
minutes duration five days per week for four weeks. The proposed volume of
training was guided by discussions with each site and reports from these [15] and other facilities [21], along with previous SMART Arm research [16,19]. All SMART Arm training and usual therapy will be recorded in
individual participant logbooks. If a participant misses a SMART Arm or usual
therapy session due to illness, medical procedure, or extended leave (e.g.,
returned to acute medical ward as became unstable), additional days will be
added to ensure all participants are given the opportunity to complete a total
of 20-days of therapy.

#### SMART Arm training

SMART Arm training will be administered for 30 minutes per day by a
physiotherapist or occupational therapist, trained in the delivery of the
intervention. The participant’s treating therapy team will administer
30 minutes of usual therapy per day. Training will be typically undertaken
five times per week for four weeks.

On commencement of a SMART Arm training session, the participant will be
seated on a (armless) chair beside the device. A harness will be applied to
restrict trunk movements to less than 15 degrees and therefore, minimise
compensatory trunk movements and encourage recovery of a pre-morbid pattern
of reaching [22-24]. The affected upper limb will be positioned in a customised
thermoplastic splint in mid pronation-supination and wrist extension (0
degrees to 45 degrees) to mimic a functional reach-to-grasp hand position [25]. To accommodate for any muscle contracture or pain, the splint
can be positioned through the full range of pronation and supination. The
splint is connected to a manipulandum, which is mounted on a linear slide
and encoder belt. The linear slide serves to constrain movement to one plane
and to reduce friction and resistance to movement. The elbow is positioned
in a standardized start position of 90 degrees of elbow flexion.

Trainers will be provided with guidelines for the administration of SMART Arm
training. To ensure participants perform a consistent minimum number of
repetitions during the training time period (30 minutes), a goal of a
minimum of 60 repetitions in week one and 80 repetitions in weeks two
through four will be set. This dose was guided by previous research [16,19]. Progression in training difficulty will occur when consistency
in task practice is evident. Training elements that can be progressed
include the number of repetitions, track elevation, degree of shoulder
external rotation, hand position, load, visual and auditory feedback,
instruction and level of supervision. The decision-making process with
regards to when and how to progress training will be at the discretion of
the SMART Arm trainer and will be based on the stroke survivor’s
performance during training. To ensure consistency between trainers,
monitoring (e.g., benchmarking evaluations of completed training logs for
consistent dose, progressions of practice used) and mentoring (e.g.,
peer-supervision, feedback during sessions, and debriefing) will regularly
occur. All SMART Arm training will be documented in a log, which will
capture dose and training element use.

##### Outcome-triggered electrical stimulation

The lateral head of triceps brachii is the target muscle of electrical
stimulation as it is the prime mover for achievement of full elbow
extension. Stimulation to triceps brachii will be delivered via an Empi
300PV unit (St Paul, MN, USA). Two surface electrodes (diameter 50 mm)
will be applied, one above the area of the triceps brachii motor point
(lateral head) and one at the muscle insertion. Stimulation parameters
will consist of a 1 second ascending ramp, and a 4 to 20 second duration
of 200-sec pulse width biphasic stimulation at 35 Hz. When training is
commenced, the participant will attempt to initiate the reaching task.
As the participants’ reach attempt surpasses their individually
determined threshold distance, electrical stimulation to triceps brachii
will be automatically triggered. The duration of stimulation provided
will be set manually to match the time required by each participant to
perform the movement. The stimulus intensity will be set to the maximum
that can be tolerated by the participant.

#### Usual therapy

Participants allocated to usual therapy alone will participate in 20 therapy
sessions of 60 minutes duration, typically undertaken five days per week for
four weeks. Usual therapy refers to the combined duration of occupational
therapy and physiotherapy. It will not be standardized and will likely
consist of a mix of individual and group sessions administering both passive
(e.g. stretching, cyclic electrical stimulation) and active (e.g. range of
movement, strengthening, modified task practice with electrical stimulation)
interventions where possible. All usual therapy will be documented in an
upper limb therapy log, which will capture dose (minutes), frequency
(sessions) and content of upper limb therapy.

